## Abstract

**Background.** Chronic kidney disease (CKD) is a leading risk factor for cardiovascular disease and all-cause mortality among older adults. Mecklenburg-West Pomerania has the highest CKD prevalence in Germany and Europe, however, its impact on frailty prevention strategies in primary care remains poorly understood. The SHIP-AGE/MV-FIT study aims to investigate the role of CKD in frailty incidence.

**Methods.** The SHIP-AGE/MV-FIT cohort is a prospective, longitudinal, population-based observational study targeting individuals ≥ 65 years with mGFR >30 mL/min. The cohort will consist of approximately 820 elderly participants who will be monitored over a three-year period. They will undergo a comprehensive, multi-factorial geriatric assessment, along with a structured monitoring and management program aimed at preventing frailty. The program incorporates evidence-based, multi-component care, including physical activity, medication review, nutritional optimization, and fall prevention strategies.

**Discussion.** SHIP-AGE/MV-FIT will clarify CKD’s role in frailty progression and identify mechanisms underlying frailty and pre-frailty. Additionally, the study aims to implement and evaluate multi-component healthcare strategies for frailty and fall prevention, assess patient adherence and quality of life, and explore elderly individuals’ experiences with primary care interventions. By integrating SHIP-AGE data with findings from the SHIP (Study of Health in Pomerania) cohorts in our region, this research will contribute to evidence-based strategies for maintaining health, independence, and well-being in aging populations, particularly in rural primary care settings, such as Mecklenburg-West Pomerania.

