### Mecklenburg-Vorpommern Frailty Observation and Interventions Trial (MV-FIT)

Our SHIP-AGE/MV-FIT study is an observational study of individuals aged 65 years or older with mGFR >30 mL/min (n=820). All participants will receive multi-component healthcare, which includes multi-factorial geriatric assessment, monitoring and management systems (Fig 3) [2, 19, 20]. Renal function (mGFR) is measured by the iohexol method. Subjects will be stratified by mGFR. The incidence of frailty is observed over 36 months. High quality biobanking of longitudinally ascertained biosamples will allow biomarker research and basic science research into ageing syndromes while performing health care research and interventional studies. All patients will be encouraged to exercise [21]. We will recommend home-based exercise programs (e.g. Go4Life program) and/or group-based exercise programs for leg strength and balance (e.g. tai chi). Participants will be advised to participate in aerobic exercise training sessions three times weekly [22]. The algorithm to guide the selection of an exercise program is provided in Ganz *et al*. [2]. All prescribed and over-the-counter drugs will be reviewed [23]. Particular attention will be paid to medications that may cause sedation, confusion, or orthostatic hypotension [23]. All medications are reviewed with a focus on advising tapering or discontinuation of nephrotoxic or potentially inappropriate medication (e.g. PRISCUS guidelines). Patients who meet the criteria for dementia or depression will be evaluated or referred for reversible causes (e.g., for management of hypothyroidism). Ophthalmological examinations are recommended every 1 to 2 years [2]. Patients with balance deficits who wear multifocal lenses may also benefit from a referral for single-lens distance glasses to use when taking part in regular outdoor activities [24]. Participants who have orthostatic hypotension will be educated about rising slowly and not ambulating immediately after standing; potentially causative medications will be recommended for potentially causative medications will be recommended for discontinuing, and adequate hydration will be encouraged [2]. If poor nutritional status, i.e. malnutrition, is detected, we will recommend nutrition counseling or referral for a dietician [25]. Participants with previous vertebral or hip fracture after minimal trauma will be offered pharmacologic treatment for osteoporosis. Dual-Energy X-ray Absorptiometry (DexaScan) assessments will be reported to all participants and the primary health care providers, i.e. family doctors. As a complement to the SHIP-AGE/MV-FIT study, we will conduct a survey on the SHIP-START/SHIP-TREND cohorts in our region [26] to gain additional epidemiological insights into frailty. Participants (approximately 2,100 individuals currently aged ≥60 years) have been longitudinally followed for up to 24 years (SHIP-START) and 12 years (SHIP-TREND). This survey will assess frailty risk factors and disease progression, leveraging long-term cohort data to enhance our understanding of aging-related health outcomes in SHIP-AGE/MV-FIT.

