
### 4. Measurements

In the SHIP-AGE/MV-FIT study we will observe 820 participants over a period of 3 years. Informed consent will be obtained for participation in the study. Subjects who consent will be screened for eligibility and if the inclusion and none of the exclusion criteria are fulfilled, subjects will be enrolled. Data obtained from the screening, and enrollment visits must be supported in the patient’s source documentation, i.e. in the geriatric health record (eCRFs). Our follow-up (visits at 1st year and every 12 months) is designed to collect these data and to strengthen compliance to the individual interventions.

Screening Visits/Baseline: Adults aged 65 years or older will be enrolled if eligible. If eGFR (CKD-EPI) is known and >25 mL/min per $1.73\;{\text{m}}^{2}$, mGFR will be measured. Scheduled examination components and timeline by visits are shown in Fig 1.

Geriatric assessments and evaluations: Tables 1 and 2 show the assessments and evaluations. The GAITRite walkway system is the current gold standard in gait analysis. Leonardo mechanography, TUG, 5CRT are other physical measures.

**Table 1 pone.0324001.t001:** Frailty, renal function, and the effect of multi-component intervention strategies.

Design:	Prospective, longitudinal, observational study
All patient intervention:	Aerobic and resistance exercise and others (multi-factorial geriatric assessment monitoring and management systems)
Inclusion criteria:	Out-patients, aged ≥65 years, mGFR ≥30 mL/min per $1.73\;{\text{m}}^{2}$
Exclusion criteria:	Bedridden, palliative, inability to consent, severe dementia (MMSE<12), inability to speak, inability to fulfill at least 60% of the assessments
Primary outcome:	Frail vs. non-Frail
Secondary:	Frailty score transition (pre-frailty), mGFR transition, patient welfare, ability to live independently (off-dialysis), quality-of-life scales, burden of CKD on health status, cognitive decline, number of falls, admission to hospitals, referrals to nursing homes, all-cause mortality in primary care
Primary statistical method:	Multivariable logistic regression
Further statistical analysis:	Multivariable Cox regression, Chi-Square-Test, Propensity score matching

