### Study outcomes

The primary outcome will be frailty at 36 months post subject inclusion (i.e. Frail vs. non-Frail). Secondary endpoints are: Frailty score transition (pre-frailty), mGFR transition, patient welfare, ability to live independently, quality-of-life scales, burden of CKD on health status, cognitive decline, number of falls, admission to hospitals, referrals to nursing homes, all-cause mortality in primary care. Secondary endpoints will be determined using a broad spectrum of standard geriatric and research assessments as shown in Table 1 (for Abbreviations: see Table 2). Identification of novel parameters may be helpful for early detection of patients at risk for falls.

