### Sample size

We performed a sample size calculation for the SHIP-AGE/MV-FIT cohort. A 3-year prevalence of frailty of 20% is expected in individuals with mGFR 30-60 mL/min per $1.73\;{\text{m}}^{2}$ and a prevalence of 12.5% in individuals with mGFR >60 ml/min/1.73 m2. The effect size of the GFR group on frailty is expressed by the odds ratio (OR) between mGFR-group 30-60 mL/min per $1.73\;{\text{m}}^{2}$ compared to the reference group mGFR >60 mL/min per $1.73\;{\text{m}}^{2}$. In multivariable adjusted models with frailty as independent variable, OR per 10 mL/min/$1.73\;{\text{m}}^{2}$ decrease of mGFR was reported to be 1.2 (Cardiovascular Heart Study) [14] and 1.4 (Modification of Diet in Renal Disease study) [18]. An OR of 1.83 was reported in multivariable logistic regression analysis when comparing mGFR 30-44 to ≥45 mL/min per $1.73\;{\text{m}}^{2}$. The target sample size was computed with G*Power by expecting a multivariable adjusted effect size of OR=1.75 in logistic regression analysis with 3-year frailty as the binary response variable. Statistical power was set to 80%, type I error rate was set to 5% and group imbalance is expected (40% will have mGFR, 30-60 mL/min per $1.73\;{\text{m}}^{2}$). Under these conditions one-sided testing led to the required sample size of 616 individuals to be analysed. To further adjust for drop-outs (lost-to-follow-up, deaths, no longer willing or capable to participate in the study), the sample size was corrected for a 25% drop-out rate justifying that 820 volunteers will be enrolled at baseline. The overall goal for recruitment is 820 participants, although the final enrolment number may be between 700 and 1,000.

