### Statistical methods

Evaluation of the impact of CKD on frailty among elderly persons The primary outcome Frail vs. non-Frail and events observed in the follow-up period will be analyzed using multivariable logistic regression. Furthermore, in case of proportional hazards, multivariable Cox regression analysis will be conducted to study the time to frail, which usually has a higher statistical power than logistic regression. Main exposure variables that enter both models are mGFR at baseline, pre-existing frails, frailty-index, sex, BMI, age, comorbidities/medical history, medication, geriatric depression score, and quality of life (see assessments). In univariable analysis all possible predictor variable will be checked in relation to the response variable whether a transformation of axis (e.g. log-transformation), spline-usage, or (re-)categorization seems appropriate and medically plausible for the use in multivariable models. In case of mGFR, we include baseline measurements, gender-specific quantile probabilities, and absolute and relative mGFR changes if available. Interaction terms will be used in model equations based on prior knowledge (evident interactions) and other (currently unknown) interaction effects will be tested for a significant increase in the model performance. Event variables (obligation to dialysis, hospital re-admission, referrals to nursing homes, all-cause mortality, etc) will be analyzed with penalized multivariable logistic regression. In order to create complete cases, we make use of imputed datasets (e.g. by Multiple imputation using Fully Conditional Specification or by Random Forest imputation). The model size will be controlled by setting regularization parameters (Elastic net or LASSO) and repeated internal cross-validation will be used to avoid overfitting and to generate more robust estimates that can result in a very generalizable model. Secondary endpoints such as the patient-individual changes in mGFR and in the frailty score will be analyzed in linear mixed effects models. Implementation of multi-component healthcare will be monitored by usage of the regional digital health records. If necessary, the results of formative process analysis are used to adapt processes or the documentation.

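### The only named time-to-frailty analysis, a supplementary Cox model, runs only if hazards are proportional, and no alternative is given

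*Protocol article*

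**What the plan says.** The aim is worded as incidence. The Abstract states "The SHIP-AGE/MV-FIT study aims to investigate the role of CKD in frailty incidence", and the MV-FIT section adds "The incidence of frailty is observed over 36 months".

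The primary endpoint is status at one time point. Under Study outcomes: "The primary outcome will be frailty at 36 months post subject inclusion (i.e. Frail vs. non-Frail".

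The Statistical methods section attaches no condition to the primary analysis: "The primary outcome Frail vs. non-Frail and events observed in the follow-up period will be analyzed using multivariable logistic regression". The time-to-onset analysis follows as an addition with a condition: "in case of proportional hazards, multivariable Cox regression analysis will be conducted to study the time to frail". The same sentence remarks that Cox regression tends to be the more powerful of the two.

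Table 1 (section 4, Measurements) names logistic regression as the primary method and lists the rest as further analysis: "Multivariable Cox regression, Chi-Square-Test, Propensity score matching". Visits are yearly, so onset is known only to the year.

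The Statistical methods section also assigns individual changes in the frailty score to linear mixed models, without condition.

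**The concern.** Proportionality of hazards can be judged only from the outcome data. A rule that fits the model only when hazards are proportional therefore makes the reporting of a result depend on that result. As the rule names no substitute, a judgement against proportionality leaves no time-to-onset analysis at all.

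The loss would not fall at random. The exposure is baseline mGFR, and the plan itself expects mGFR to change during follow-up (it is a secondary endpoint), so a CKD effect that builds up over three years is plausible. That pattern would be a scientific finding, yet under this rule it removes the analysis that would show it. Timing information from the 12- and 24-month visits, and the observed frailty-free follow-up of people who later drop out, enter a time-to-onset model only through the Cox regression.

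What is at stake is selective reporting of a secondary result, not the primary comparison.

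**Working it through.** **Inputs from the protocol (Sample size, unless noted).** "A 3-year prevalence of frailty of 20% is expected in individuals with mGFR 30-60 mL/min"; "a prevalence of 12.5% in individuals with mGFR >60"; 40% of participants in the lower mGFR group; odds ratio 1.75; one-sided 5%; 80% power; 616 analysed; 25% drop-out; 820 enrolled. Yearly visits (Measurements). The article states no test or threshold for proportionality, so every drop rate below assumes a 5% test.

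**1. Reproduce the plan's own figure.**
- Odds ratio: (0.20/0.80) / (0.125/0.875) = 1.75, as stated.
- One-sided two-proportion formula, allocation 2:3, pooled proportion 0.4 × 0.20 + 0.6 × 0.125 = 0.155. Reference group = [1.645 × √(2.5 × 0.155 × 0.845) + 0.842 × √(0.125 × 0.875 + 1.5 × 0.20 × 0.80)]² / 0.075² = 368. Total 368/0.6 = 614, against 616 stated.
- Drop-out: 616/0.75 = 822, against 820 stated (820 × 0.75 = 615).

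The study is therefore sized on the unconditional 36-month logistic analysis.

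**2. Would dropping Cox cost the main comparison anything?** Assume nobody is frail at baseline and hazards are constant.
- Hazard ratio = ln(0.80)/ln(0.875) = 1.67.
- Events = 616 × 0.155 = 95.
- Schoenfeld power, one-sided = Φ(√(95.48 × 0.4 × 0.6) × ln 1.67 − 1.645) = Φ(0.81) = 79.2%.
- Power of the 36-month binary comparison = 80.2%.

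In this illustration Cox has no power advantage. What disappears is the information on timing.

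**3. How often would the rule drop the analysis?** Simulation: 1,000 data sets, 616 people, three yearly visits, 12.5% against 20% frail by 36 months, 5% test of group-by-time on the complementary log-log scale. The reference hazard is 0.1335/3 = 0.0445 per year. The CKD group's cumulative hazard of 0.2231 is split over the three years as shown.

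| Split of CKD hazard | Yearly hazard ratios | Cox dropped | Logistic power |
|---|---|---|---|
| Constant | 1.67 throughout | 4.5% | 78.5% |
| 20/33/47% | 1.00 / 1.65 / 2.36 | 35% | 79.6% |
| 10/30/60% | 0.50 / 1.50 / 3.01 | 88% | 80.3% |

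**4. Sensitivity to the form of the check.** These results come from models with ten terms, 820 people, annual visits and 25% drop-out (400 data sets each).
- Hazards truly proportional: a global test rejected in 4–4.5% and the mGFR term alone in 6%.
- Yearly hazard ratios 1.00/1.65/2.36: the CKD term rejected in 41% and a global test in 18%.

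**5. Precision of year-specific estimates.** 95/3 ≈ 32 events per year. The standard error of the log hazard ratio ≈ 1/√(31.8 × 0.24) = 0.36, so the 95% limits lie a factor exp(1.96 × 0.36) ≈ 2.0 either side. For all 95 events the factor is exp(1.96/√22.9) ≈ 1.5.

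**The case against.** **The primary analysis does not depend on the condition.** This stands. A reader might infer that the condition decides whether frailty over 36 months is analysed at all. The documents do not support that: logistic regression of 36-month status is the named primary method, carries no condition and is the basis of the sample size. Nor is what remains a selected result, because it is the pre-declared comparison with its power intact. Keeping people who are frail at baseline, with adjustment, does raise the question whether the logistic model targets pure incidence, but that is separate from proportional hazards.

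**The course of frailty is still analysed.** This stands too. Mixed models of the frailty score can use the annual visits. They do not model time to onset, so the gap is confined to that.

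**The check may be harmless.** A reader might infer from the ten listed predictors that one chance rejection would remove the analysis in 1 − 0.95¹⁰ = 40% of studies with proportional hazards (33% and 43% in two simulations). That assumes each term is tested separately at 5% and that any single rejection abandons the model. The article states no such rule.

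**Such detail belongs in the analysis plan.** Partly right. A missing test or threshold is no finding in a condensed article. But the article does more than omit a detail: it states a condition. An analysis plan that follows it inherits the condition, and one that always fits the model departs from it.

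**A single hazard ratio misleads when hazards diverge.** True, but that argues for a time-varying effect, not for having no analysis.

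**Conclusion.** The concern holds for a supplementary analysis. As written, reporting of the only named time-to-frailty result depends on the data, and the result is most likely to be lost when the CKD effect changes over time. With truly proportional hazards the loss is small, about 4–6% under a global or mGFR-only 5% test. With a growing CKD effect, a test of that effect loses the analysis in 35–88% of studies under the two patterns examined; a global test loses it in 18% under the milder one.

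These rates rest on an assumed 5% test, nobody frail at baseline and the protocol's expected frailty rates. That the text implies a formal pre-test is itself an inference. The point is worth correcting because the change is cheap, but it gives no reason to doubt the primary analysis or the sample size.

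**What to change.** Delete the condition and commit to fitting the time-to-frailty model in every case, preferably as a discrete-time (complementary log-log) or interval-censored model, since onset is observed only at yearly visits. Report the proportionality check as a diagnostic that does not decide whether results appear. State in advance that, if the CKD effect appears non-proportional, a CKD-by-interval term will be added and the adjusted 36-month cumulative incidence difference reported.

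The cost is a short change to the Statistical methods section and no new data. Recruitment began on 3 April 2024, so at the article's status date of 5 March 2025 no participant could have reached 36 months. The real downside is precision: with roughly 30 events behind each year-specific hazard ratio, these estimates should be labelled descriptive.

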9. Blood pressure	Seated Blood Pressure/Pulse velocity	
10. Orthostatic Hypotension	Standing Blood Pressure/Tilt table/Finapres Nova^®^	Finapres
	Symptoms of orthostatic hypotension	
11. Nutrition	Mini Nutritional Assessment	MNA
	Nutrition protocols, Veggie Meter^®^	
12. Health related quality of life	Health-related quality of life	HRQL
	Geriatric depression scale	GDS
	Generic health status	EQ-5D-5L
	Health related quality of life questionnaire	QOL
	12-Item Short Form survey	SF-12
13. Dementia Screening	Mini Mental State Examination	MMSE
	Verbal learning and memory test	VLMT
	Money counting test	
	Watch test	
14. Laboratory	Blood and Urine Collection	

Schedule of Follow-Up Visits and Procedures by Visit: Post-enrolment follow-up visit schedules for data collection do not differ between both mGFR groups. All participants will have post-enrolment visits every 12 months thereafter (Fig 1). The trial is testing the effectiveness of a treatment strategy question regarding the burden of CKD on frailty and all its consequences on health status in the elderly and not testing specific treatments. All subjects will undergo multi-component digital intervention strategies, which include multi-factorial geriatric assessment, monitoring and management systems intervention and eHealth (Fig 3). The intervention protocol is strict in medical advice and interventional details. However, it is flexible in terms of choice of individual treatments (i.e. acceptance to implement recommendations, environmental assessments and modification, extent and degree of aerobic and/or resistance exercise, single-lens distance glasses for outdoor activities etc.). Multi-component compliance will be monitored and studied in regression model to analyse the implementation of the individual interventions. Our follow-up (visits at 1st year and at least every 12 months) is designed to collect these data and to strengthen compliance to the individual interventions. We will follow the participants with geriatric health records to document the objectives.

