### Eligibility criteria

Inclusion/exclusion criteria were made as simple as possible to recruit a largely heterogeneous (“real world”) elderly population.

Inclusion Criteria: Age 65 years or older, mGFR >30 mL/min per $1.73\;{\text{m}}^{2}$, being able to understand and give written informed consent.Exclusion Criteria: Bedridden, palliative, inability to consent, severe dementia, inability to speak, lack of compliance (paracusis, inability to fulfill at least 60% of the assessments).

Recruitment is promoted through various regional media and communication channels. These include advertisements in local newspapers, publications in municipal bulletins, flyers, and information on websites and digital platforms. Additionally, local networks and community structures are utilized to reach interested older adults and encourage broad participation. We will establish networks with ambulatory practices and stakeholders to recruit and follow the patients. In terms of CKD patients, we will contact local nephrologists in practice. All sites are located in MV.

Participants will be stratified by mGFR: into (a) individuals with mGFR, 30-60 mL/min per 1.73 m2 or urine albumin/creatinine ratio (UAC) ≥300 mg/g and (b) individuals with mGFR, >60 mL/min per $1.73\;{\text{m}}^{2}$ and urine albumin/creatinine ratio (UAC) <300 mg/g. Approximately 328 participants (40%) are expected to have mGFR, 30-60 mL/min per $1.73\;{\text{m}}^{2}$ and 492 participants (60%) are expected to have mGFR, >60 ml/min/$1.73\;{\text{m}}^{2}$ (Fig 2). The planned minimum follow-up duration for participants is three years, while the maximum follow-up duration is approximately six years.

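### Participants already frail at entry stay in the time-to-frail model and in the 36-month logistic model, so neither estimates the effect of kidney function on incident frailty

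*Protocol article*

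**What the plan says.** The Abstract gives the aim: "The SHIP-AGE/MV-FIT study aims to investigate the role of CKD in frailty incidence". The MV-FIT section repeats it: "The incidence of frailty is observed over 36 months".

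Study outcomes defines something different, a status at one time point: "The primary outcome will be frailty at 36 months post subject inclusion (i.e. Frail vs. non-Frail". The Sample size section likewise uses a 3-year prevalence of frailty, 20% with mGFR 30-60 and 12.5% with mGFR above 60.

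Eligibility does not require participants to be non-frail. Inclusion starts with "Age 65 years or older, mGFR >30 mL/min per" 1.73 m² and adds only capacity to consent. The exclusions are "Bedridden, palliative, inability to consent, severe dementia, inability to speak, lack of compliance", the last of these explained as hearing problems or failure to complete enough of the assessments. Table 1 gives essentially the same list.

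Statistical methods then puts baseline frailty into the models: "Main exposure variables that enter both models are mGFR at baseline, pre-existing frails, frailty-index, sex, BMI, age", followed by comorbidity, medication and other variables. Table 1 also lists it as a main confounder. The second of the two models is the Cox model: "multivariable Cox regression analysis will be conducted to study the time to frail, which usually has a higher statistical power than logistic regression". On visits, section 4 (Measurements) says "All participants will have post-enrolment visits every 12 months thereafter".

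**The concern.** A covariate for pre-existing frailty can vary only if people who were frail at entry are in the analysis set. The text therefore places them in both models; this is not a detail left open for an analysis plan.

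In the Cox model the consequence is direct. Someone already frail has no time to first frailty and does not belong in the risk set for onset. Adjusting for baseline status changes the linear predictor, not who is counted as at risk, so the hazard ratio would not be an effect on becoming frail.

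In the logistic model, the outcome is onset for a participant non-frail at entry, and persistence or recovery for one already frail. Without an interaction between mGFR and baseline frailty, one mGFR odds ratio averages the two. Recovery is plausible here, because every participant is offered a programme meant to reduce frailty. Reporting that odds ratio as the role of CKD in frailty incidence would answer a question the model did not ask.

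**Working it through.** **1. The plan's own sample size.** Inputs from Sample size: 20% versus 12.5%, 40:60 split, one-sided 5%, power 80%. The odds ratio is (0.20/0.80)/(0.125/0.875) = 1.75, as stated. The two-proportion formula gives 246 in the 40% group, so 246 × 2.5 = 615 in total, against 616 stated. Power at 616 (246.4 and 369.6 per group): se0 = √(0.155 × 0.845 × (1/246.4 + 1/369.6)) = 0.0298; se1 = √(0.16/246.4 + 0.1094/369.6) = 0.0307; (0.075 − 1.645 × 0.0298)/0.0307 = 0.85, which is 80%. The arithmetic is sound. It concerns prevalence at 36 months, old and new cases together.

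**2. Expected frail cases at 36 months.** 616 × (0.4 × 0.20 + 0.6 × 0.125) = 616 × 0.155 = 95.5.

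**3. Carried-over cases.** Let f be baseline frailty and s the share of those people still frail at 36 months. Neither is given for this cohort. Assumed range for f: 2.5% to 7%. The Introduction's background figures are 2.5% (men) and 3.1% (women) in German cohorts, and 341/4,987 = 6.8% in a US community cohort aged 66 or older. Assumed range for s: 50% to 100%.

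- Low end: 616 × 0.025 × 0.5 = 7.7 cases, 8% of 95.5.
- High end: 616 × 0.07 × 1.0 = 43.1 cases, 45% of 95.5.
- German figures only: 7.7 to 616 × 0.031 × 1.0 = 19.1 cases, 8% to 20%.

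The at-risk set is 616 × (1 − f), about 601 to 573. Incident cases are 95.5 minus those carried over, about 88 to 52.

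**4. Power for incident frailty.** In group g with 36-month prevalence p and baseline frailty f, incidence is (p − s·f)/(1 − f). This counts only new cases still frail at 36 months. The power formula of step 1 is applied to the reduced groups under two assumptions about baseline frailty.

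Example (f = 7%, s = 100%, baseline odds ratio 1.75 between groups): baseline frailty is 9.25% and 5.50%, since 0.4 × 9.25 + 0.6 × 5.50 = 7.0. Incidence is (0.20 − 0.0925)/0.9075 = 11.85% and (0.125 − 0.055)/0.945 = 7.41%. At-risk numbers are 223.6 and 349.3. Power is 56%.

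| f | s | Power, baseline OR 1.75 | Power, equal baseline frailty |
|---|---|---|---|
| 2.5% | 50% | 78% | 83% |
| 2.5% | 100% | 73% | 85% |
| 7% | 50% | 74% | 87% |
| 7% | 100% | 56% | 94% |

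The columns diverge because the planning prevalences are held fixed. If the gap between groups already exists at baseline, part of the 7.5 points is removed with the prevalent cases, and the odds ratio among those at risk is about 1.68 to 1.77. If baseline frailty is equal, the whole gap must arise from new cases, and that odds ratio is about 1.83 to 2.59.

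**The case against.** The strongest reply is that the primary analysis is coherent on its own terms. The outcome is status at 36 months, the sample size uses prevalence, and regressing follow-up status on exposure and baseline status is a standard analysis. Objective 1 speaks of the impact of CKD on frailty generally, and the programme is meant to reduce frailty in everyone, so persistence and recovery matter too. This stands. A reader might infer that the primary logistic analysis is invalid; the documents do not support that. The conflict is with the incidence aim, not with the outcome definition.

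A reader might also infer that the study is underpowered. That does not follow: the loss appears only if the kidney-function gradient is assumed to be present at baseline, and no figure for this cohort settles that.

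Thirdly, annual visits suggest just three tied event times. This is not fixed either. Eligibility criteria allows follow-up to about six years, and section 4 says visits occur at least every 12 months. Handling of ties can reasonably be left to an analysis plan.

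Lastly, the Cox model is listed as a further analysis and depends on proportional hazards. Frailty-score transition is a secondary endpoint with a mixed model, and interactions are foreseen in general. None of this removes the already frail from the time-to-frail risk set, and no interaction of mGFR with baseline frailty is named.

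**Conclusion.** The point holds in this form: followed as written, the plan keeps baseline-frail participants in both models. The Cox analysis then includes people who are not at risk of its event, and the logistic odds ratio mixes onset with persistence. Neither can carry a conclusion on incident frailty. This rests on the text alone and needs no numerical assumption.

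The size is illustrative. About 8 to 43 of some 95 expected frail cases would be carried over, given 2.5% to 7% baseline frailty and 50% to 100% persistence; the German background figures sit at the lower end. Power for incident frailty at 616 analysed ranges from 56% to 94% across the scenarios, so no loss of power can be asserted, only that it is unchecked. Nor does the argument require the frailty index to be removed: it is listed separately from pre-existing frailty and can still vary among people who are not frail.

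**What to change.** - Restrict the time-to-frail analysis, and whichever analysis supports an incidence conclusion, to participants not frail at baseline.
- In those models drop the pre-existing-frailty covariate, which is then constant. Keep pre-frailty or the frailty index as baseline adjustment.
- Report the baseline-frail separately, as persistence or recovery.
- If baseline-adjusted 36-month status stays the primary outcome, say so and do not call it incidence.
- Re-check power on the at-risk set, using the observed baseline frailty by mGFR group once enrolment is complete.
- Since frailty is assessed at roughly annual visits, a discrete-time (grouped) model is a reasonable option for time to frail, not a necessity.

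Cost: no new data. The analysis set shrinks slightly, by about 15 to 43 of 616 at 2.5% to 7% baseline frailty, and a protocol amendment is needed, for which the article says new approval will be sought. With 505 enrolled by March 2025 and completion estimated for September 2030, the change can precede the 36-month analysis.
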